## **ETHICAL CONSIDERATIONS**

Full medical confidentiality will be preserved. The study will be conducted according to ICH GCP guidelines and the Declaration of Helsinki (version 2002), and it is the responsibility of the Clinical Investigators to ensure adherence. Before the study starts all personnel involved in the clinical and laboratory trial units will be trained for Good Clinical Practice (GCP) and/or Good Laboratory Practice (GLP) respectively. Study personnel will also be trained on standard operating procedures (SOPs) that are related to the protocol and will follow the GCP and GLP guidelines.

This protocol has been reviewed by WHO VAC advisory board. It has also been submitted to the national ethical committees in Tanzania, ie, National Institute of Medical Research (NIMR) and after receiving approvals from NIMR will then be submitted to the institutional ethical committee at Muhimbili University College of Health Sciences (MUHAS) and subsequently to the appropriate ethics committee in Sweden. The DNA and MVA vaccines which will be donated by the Karolinska Institute in Sweden have been approved by the Swedish Medical Products Agency and are currently used in the ongoing clinical trials in Sweden. The US Food and Drug Authority has previously approved the MVA which is in ongoing clinical trials in the USA. Approval of these immunogens will also be undertaken independently by the Tanzania Food and Drug Authority (TFDA).

The Principal and Clinical Investigators are also responsible for informing the ethics committees of any SAEs as required, and submitting annual reports as required. No study materials will be obtained from study volunteers before approval from the relevant bodies. The Karolinska institute in Sweden will be responsible for providing the Investigator's Brochure (IB) for DNA as well as the Investigator's brochure for MVA.

The TCC will be responsible for preparing the randomisation list, all aspects of data management including monitoring of the clinical sites, and the analysis. Staff will also be responsible for coordinating the response to any SAEs that arise during the course of the trial and reporting these if indicated to the regulatory authorities.

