## **METHODOLOGY**

### **Study design**

This is a randomised, controlled, double blinded study. The laboratory staff will also be blinded to the immunization regimens.

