The **second screening visit** (study visit 2) takes place two to four weeks before the first planned injection. This visit will include review of all laboratory results. At this visit the study nurse confirms that the volunteer fulfils all the inclusion criteria, including laboratory results, makes an abbreviated risk assessment and a brief summary of the study design. Reassurance has to be made that the study volunteer fully understands the concept of the study. The results of the screening investigations will be reviewed and volunteers who are still eligible and willing will be asked to donate blood samples for baseline immunogenicity and complete part 2 of the Informed consent (*Appendix ii/iv, CRF 4-II*). Volunteers will also be reminded that they are free to end all obligations in the study whenever they wish and that a premature termination will not have any negative influence in future contacts with the clinic. If no contraindications are revealed volunteer will be asked to donate blood for first baseline immunogenicity tests.

The volunteer will then be randomized into one of the study arms. At randomization a total of sixty sealed plain envelopes containing an equal number of assignments to groups I, II and IIIa & IIIb, will be prepared and put in the box. Group numbers refer to the immunization schedule.

The study Pharmacist will take the prepared envelopes and put them in the box that is kept under lock. Volunteers accepted into the study will be randomized by a Pharmacist through CRF7-I, by selecting the next consecutive envelope containing the vaccine or placebo assignment in accordance with the generated randomization list. This will be documented in CRF 7-II.

The Pharmacist will then inform the Study Nurse at the clinic of the randomization group of the volunteer (ID or IM) on a copy of CRF 7-I, including a number of the envelope, but will not inform on whether this is vaccine or placebo. The Study Nurse will record the envelope number and the IM/ID assignment into a Register book, the medical record file (source document), as well as the outer cover of the volunteer's file.

The pharmacist will then deliver to the nurse the appropriate vaccine/placebo that corresponds to the assigned group.

Recruitment of volunteers will be staggered so that a maximum of 3 volunteers per week will enter the trial during the first 5 weeks.

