### **Blinding procedure & Study visits**

The vaccines will be kept in the department of Microbiology/Immunology, MUHAS and the pharmacy under appropriate storage conditions according to manufacturer's specifications. One identified pharmacist who has access to the code will draw the study vaccine and the reference vaccine into syringes and label them with three initials and study number and hand them over to the study nurse for injection. All samples from the volunteers will be labeled using three initials and study numbers. Nurses administering the vaccines together with all other investigators who will be involved in the follow up process as well as the volunteers themselves will be blinded to the type of vaccine that the volunteer will be receiving.

**Week 2 (study visit 4)** is conducted by the study nurse(s) and the study doctor. Study form CRF 8-II is filled in and blood donated according to flow chart. Any medications taken will be filled in CRF 9. Abbreviated risk assessment and risk behaviour counseling will be done.

**Week 4 (study visit 5)** the visit for the second injection of the study vaccine, is conducted by both the study nurse and the study doctor. Before injection the diaries over events after the last injection will be discussed with the study volunteer and an abbreviated risk assessment and risk behaviour counseling will be performed. Urine for pregnancy test will be performed and found negative. Enough time has to be planned for the visit so that all questions from the volunteer about the study can be answered or reflected upon. After blood donation the second injection is given and the visit is documented in study form CRF 8-II. Again volunteers will be observed for 30 minutes following injection and new diaries over events will be issued for recording events over 7 days.

**Week 6 (study visit 6)** is conducted by the study nurse(s) and the study doctor. Study form CRF 8-II is filled in and blood donated according to flow chart. Abbreviated risk assessment and risk behaviour counseling will be done.

**Week 8 (study visit 7)** is conducted by the study nurse(s) and the study doctor. Diaries over events after the last injection will be discussed with the study volunteer. Study form CRF 8-II is

filled in and blood donated according to flow chart. Urine for pregnancy test will be performed and found negative. Abbreviated risk assessment and risk behaviour counseling will be done.

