Safety and Immunogenicity will be assessed at 2 weeks, 1 month, 2 months and 6 months post 2nd MVA.

Between the 1st and 2nd MVA/Placebo vaccinations consenting volunteers will attend the clinic at 8 weeks intervals with a standard follow up. Whenever appropriate, volunteers will also be invited to meetings with the investigators and representatives of the Community Advisory Board aimed at emphasizing low risk behavior towards HIV and AIDS as well as giving updates on matters relating to HIV vaccine trials and HIV and AIDS in general. It will also be an opportunity to maintain contacts with the volunteers and enable the volunteers to share experiences on being in the trial.

**Week 76 (study visit 17)**, this visit will be held four weeks before the 2nd MVA/placebo vaccination, for those who would have given consent during visit 16. Blood will be donated for ELISA HIV testing and for HIV DNA or RNA PCR for those found to have HIV antibodies by ELISA in order to determine if seropositivity is due to HIV acquisition or is a result of candidate HIV vaccine immunogenicity.

**Week 78 (study visit 18)**, this visit will be held two weeks before 2nd MVA vaccination. Volunteers will be given their HIV test results, and those found HIV negative will be invited for 2nd MVA at visit 19. Abreviated risk assessment and appropriate counseling will be conducted

**Week 80 (study visit 19)**, the visit for the second MVA injection of the study vaccine, is conducted by both the study nurse and the study doctor. Before injection the diaries over events after the last injection will be discussed with the study volunteers and an abbreviated risk assessment and risk behaviour counseling will be performed.

Urine for pregnancy test will be performed on female volunteers .

Enough time has to be planned for the visit so that all questions from the volunteers about the study can be answered or reflected upon. Blood will be donated for immunogenicity. The MVA injection is then given and the visit is documented in study form CRF 8-II. Again volunteers will be observed for 30 minutes following injection and new diaries over events for 7 days will be issued.

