#### **Dispensing records and disposal of unused product**

The designated pharmacist will, upon receipt of supplies prior to commencement of the trial, conduct an inventory and complete a receipt, one copy of which will be retained at the site, and the original returned to the supplier (Karolinska Institute, Sweden). During the trial the pharmacist will be responsible for reviewing the dispensing log. On the day of immunization the study nurse will fill in the request form with the study number, date of birth, and immunization number. Upon receipt of the syringes with the vaccine from the pharmacist, the study nurse will deliver the vaccine. The immunization number and date will be entered against the study number in the dispensing log. The vial label will be cross-checked against the details on the prescription and dispensing log by two individuals (pharmacist and nurse), prior to the vaccine/placebo being administered.

The Pharmacist will be responsible for ensuring that the return of used vials is recorded in the dispensing log at the end of the clinical session, and that they are placed in the appropriate volunteer carton. At the end of the trial all used and unused vials will be checked against the inventory by the monitor before disposal on site according to MNH biohazard regulations. Documentation of disposal will be provided to the monitor and supplier. During the trial, product accountability will be monitored by the prescriptions, the dispensing log, the returns, the trial register and data collected on the clinical research forms.

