## **TRIAL COMMITTEES**

### **Trial Coordinating Committee (TCC)**

The supervision of the trial will be a responsibility of the Trial Coordinating Committee (TCC). The committee will have an independent chair and a secretary. The members will include the 2 Principal Investigators, study director, clinical co-ordinator, laboratory co-ordinator, study nurse and data manager. The TCC will be meeting at least once a week during the trial period. The TCC will prepare a monthly report for presentation at the HIVIS governing board meeting. This committee will be responsible for final decisions about grade of adverse events and relationship to study vaccine. Notes of meetings will be kept, and the Committee will report to the HIVIS Project Governing Board. The trial may be terminated by this Committee for any reason, including on the recommendation of the DSMB.

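### The protocol's double-blind is contradicted by its own text: the committee with the final say on adverse events also prepares the randomisation list, and the nurse checks the vial label

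*Protocol*

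**What the plan says.** The Study design section declares the blind: "This is a randomised, controlled, double blinded study", with laboratory staff blinded too. Blinding procedure & Study visits says how it is kept. Code access sits with a single pharmacist: "One identified pharmacist who has access to the code will draw the study vaccine and the reference vaccine into syringes". The syringes are labelled with initials and study number before they reach the nurse. Those kept blind are "Nurses administering the vaccines together with all other investigators who will be involved in the follow up process", as well as the volunteers. The description of the second screening visit agrees: the pharmacist tells the nurse the route and the envelope number, "but will not inform on whether this is vaccine or placebo".

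Three other places pull the other way.

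- **Ethical Considerations:** "The TCC will be responsible for preparing the randomisation list", along with data management and the analysis. The TCC section lists as members the two principal investigators, the study director, the clinical and laboratory co-ordinators, the study nurse and the data manager. It adds: "This committee will be responsible for final decisions about grade of adverse events and relationship to study vaccine".
- **Dispensing records and disposal of unused product:** "The vial label will be cross-checked against the details on the prescription and dispensing log by two individuals (pharmacist and nurse", before the product is given. The same section has the study nurse give the injection.
- **HIV testing (Clinical Management):** ELISA is run in real time at weeks 40, 60, 76 and 104, with PCR if reactive, so that volunteers can be told before the trial ends. The week 78 visit, two weeks before the second MVA, states: "Volunteers will be given their HIV test results, and those found HIV negative will be invited for" the second MVA.

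**The concern.** Safety is a primary endpoint, and much of it is judged rather than measured. Volunteers grade injection-site pain, chills, headache, nausea, malaise and myalgia; staff verify grade 3 and 4 events; relatedness is a clinical opinion. Adverse-event rates are then compared between arms by Fisher's exact test, with 40 volunteers on vaccine and 20 on placebo. At that size a few events graded or attributed differently can change the comparison, in either direction.

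The blind is what protects such endpoints. If the people who settle grade and relatedness are also responsible for the list, or if the nurse who injects and later records reactions can read the product from a label, the protection depends on local practice and not on the protocol. The laboratory co-ordinator's seat on the committee raises the same question for the immunogenicity endpoints, because laboratory staff are meant to be blind.

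**Working it through.** The plan gives no figure on this point to reproduce. The check is a comparison of passages, followed by three short calculations.

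**1. Who must be blind, and who has a route to the allocation**

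| Role | Blinding text | Conflicting text |
|---|---|---|
| Principal investigators, clinical co-ordinator | Blind, if involved in follow-up | TCC members; the TCC prepares the list |
| Laboratory co-ordinator | Laboratory staff blind | TCC member |
| Study nurse | Blind; told route and envelope number only | TCC member; the nurse cross-checks the vial label |
| Data manager | Not named | TCC member; the TCC is responsible for list, data management and analysis |
| Pharmacist | Named code holder | None |

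**2. Who decides on adverse events**

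The Analysis paragraph of the Statistical Considerations sets the order: the Clinical Investigator grades, the Trial Management Group reviews, and queries that stay unresolved go to the TCC. The core members of the Trial Management Group are the clinical co-ordinator, study nurse and data manager, and all three also sit on the TCC. So the middle tier is not separate from the body responsible for the list. No delegate, sealed copy or restricted access within the TCC is described.

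**3. What can still be protected**

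- Enrolled: 60. First MVA or placebo given by 19 May 2008: 26.
- First MVA or placebo outstanding: 60 − 26 = 34. Second outstanding: up to 60.
- Total outstanding: 34 + 60 = 94 of 2 × 60 = 120, and 94/120 = 78%.
- All planned injections: 5 × 60 = 300 (three DNA, two MVA), and 94/300 = 31%.

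By that date 57 of 60 had received all three DNA or placebo doses. The 94 leaves out the few DNA doses that may still have been due to the other three.

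**4. What a disclosed HIV result would reveal**

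The protocol says that vaccination itself can turn a commercial ELISA positive. Within each route the split is 20 vaccine to 10 placebo, so the prior probability of vaccine is 20/30 = 0.67. Let s be the ELISA-positive share among uninfected vaccinees and f the share among uninfected placebo recipients. Given a reactive ELISA with negative PCR,

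P(vaccine) = (2/3)s / [(2/3)s + (1/3)f].

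The documents give neither rate; these are assumptions.

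| f | s = 0.10 | s = 0.50 | s = 0.90 |
|---|---|---|---|
| 0.01 | 0.952 | 0.990 | 0.994 |
| 0.05 | 0.800 | 0.952 | 0.973 |

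**5. When that could matter**

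The first real-time test after vaccination is at week 40. The DNA doses fall at weeks 0, 4 and 12 and the first MVA at week 36, so their 7-day diaries are complete before then. Only the fifth injection, at week 80, is exposed by this route. The Antibody responses section lists serology at screening and weeks 60 and 76, which differs from the HIV testing section, but both include weeks 60 and 76, before that dose.

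**The case against.** The strongest reply is that no breach is shown. The blinding section says plainly that nurses and follow-up investigators are blind, envelopes are sealed and locked away, and one pharmacist has access to the code. Being responsible for the list may mean oversight: the same sentence makes the TCC responsible for data management and site monitoring, which other sections give to a data manager and an appointed monitor. The TCC has an independent chair, only unresolved queries reach it under the analysis text, and the DSMB assesses relatedness for stopping. All of this stands against a claim of actual unblinding. It does not remove the conflict, because no sentence separates the list from the members who judge events.

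Four stronger readings are tempting, and the documents do not support them:

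- **That the assessors know the allocation.** No passage says that any TCC member sees the list.
- **That the vial label names the product.** For the DNA product the Labels section refers only to pre-labelling under standard procedures. That the nurse who checks is also the one who injects is the natural reading, but it is not stated outright.
- **That volunteers are told they are ELISA-reactive but PCR-negative.** The week 78 text speaks only of their HIV test results, and the participation card goes to every volunteer, so it reveals nothing about arm.
- **That 78% of the trial is at stake.** That share counts MVA-stage injections only.

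It is also fair that all 60 volunteers are enrolled, so the list cannot usefully be produced afresh elsewhere. Control of access to it can still be fixed.

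**Conclusion.** The contradiction is real and lies in the protocol's own wording. The blinding text confines the code to one pharmacist; the ethics text gives the list to a committee of investigators and site staff that also settles adverse-event grade and relatedness; and the dispensing text brings the nurse to the vial label with no masking described. Following the document as written can therefore break the blind on subjective primary safety endpoints. Actual unblinding is not shown, and the size and direction of any bias cannot be estimated from the documents.

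The part that can still be protected is up to 94 injections, about 31% of the 300 planned, assuming no withdrawals and the position at 19 May 2008.

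The HIV-result route is a secondary matter. A disclosed reactive, PCR-negative result would point strongly to vaccine (0.80 to 0.99 over the assumed rates), but the number of volunteers affected is not given, disclosure in that form is not stated, and the reactogenicity data of the first four injections cannot be affected. Testing during the trial is needed for the volunteers; what is missing is agreement between the testing text and the blinding text.

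**What to change.** 1. **Ethical Considerations.** State that the existing randomisation list is sealed and held only by the unblinded pharmacist, or by a person with no role in follow-up. Document who has had access so far. Exclude anyone who has seen the list from adverse-event grading and causality decisions, in the TCC and in the Trial Management Group. Make the TCC section and the Analysis paragraph agree on which decisions reach the TCC.
2. **Dispensing records.** Have the nurse check only the coded syringe (initials and study number) against the request, and the pharmacist alone check the product label. This matches the blinding section as it stands.
3. **HIV testing.** Reconcile the week 78 visit, the Antibody responses section and the HIV testing section with each other on test weeks, and with the blinding section on what is released and to whom before the second MVA. The content of that rule is for the sponsor and the investigators, who must also weigh volunteers' access to their own results.

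The cost is protocol and procedure wording plus an access log. The pharmacist already holds the code and prepares the syringes, so no new role is needed unless the access log shows that a current assessor has seen the list and must be replaced for grading.

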## **INDEMNITY**

### *Insurance for investigators*

The Principal Investigator will ensure that relevant clinical and laboratory staff engaged in the study are covered for possible legal actions against the investigators for harm through indemnity insurance schemes which will be paid for by the project during the study period.

### *Health care Insurance for trial volunteers*

All trial volunteers will be provided with health insurance cover for injury or death related to the trial through insurance schemes.

Vecura company in Sweden will have an insurance that covers any defect in the production of the immunogen.

### **PROTOCOL AMENDMENTS**

The TCC will be responsible for preparing protocol amendments needed by the HIVIS governing board. Amendments to the protocol will be made only after consultation and agreement between sponsors and Principal investigators. The only exception is where the study director considers that a volunteer's safety is compromised without immediate action. All amendments that have an impact on volunteer risk or the study objectives, or require revision of the informed consent document, must receive approval from the relevant ethical committees prior to their implementation.

### **PUBLICATION**

It is intended that the results of this study will be published in an appropriate peer-reviewed journal, with the aim of submitting a paper for publication within 6 months of the study's completion.

The HIVIS Trial Coordinating Committee and Bioject Inc will have 30 days to comment on any manuscript. No other publications, whether in writing or verbally, will be made before the definitive manuscript has been agreed and accepted for publication, without the prior approval of this committee. A final report of the study will be prepared by the Investigators and circulated to the HIVIS governing board for comments.

The presenting author for the first conference presentation of the main trial results will be one of the Tanzanian principal investigators or their deputy.

